### Sample size

The primary analysis for the RCT will be a comparison of the unweighted mean number of child material and social deprivation (MSD) items lacked (T2). The target sample size has been calculated based on this primary analysis. The power calculation has been informed by child MSD data for Sweden collected via the European Union Statistics on Income and Living Conditions (EU-SILC) survey, which reports an unweighted mean of 4.5 items lacked among the materially-deprived population. Using a significance level of 0.05 and 80% power, a total of 142 families (71 per group) will be required to detect a 1-item group difference in the unweighted mean number of child MSD items lacked, assuming a standard deviation of 3. As the trial will be conducted in areas with high rates of socioeconomic disadvantage, we estimate that up to 30% of families will experience financial hardship and be eligible for inclusion. The estimated rate of uptake is 50% among eligible families, based on a pilot in the Sandviken municipality, Sweden. Loss to follow-up is projected at 50%. See Fig. 2 for the participant timeline with projected numbers.

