## Method

### Design

A two-arm randomised waitlist-control superiority trial (1:1 allocation ratio) will be conducted to evaluate the effectiveness of the HWF model in improving the financial situation of families who have self-reported economic difficulties. The intervention arm will be referred to budget and debt counselling immediately after randomisation and the waitlist-control arm 3 months later. Informed by Patient and Public Involvement (PPI), so all participants receive some form of support at randomisation, both arms will be offered a freely available financial guidance book. RCT assessments will take place at two points: pre-intervention (T1) and post-intervention (T2; 3 months after randomisation).

A longitudinal cohort study will be conducted with all participants, from both trial arms (intervention and waitlist-control). Longitudinal assessment will take place 12 months after randomisation (T3), to assess any changes in measures between T2 and T3. See Fig. 2 for the participant timeline.

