### Statistical methods

Baseline and demographic characteristics will be summarised using means and standard deviations (or medians and interquartile ranges) for continuous variables and percentages for categorical variables. For items that align with national survey questions, population-level comparisons will be made. Descriptive data will also be reported on process outcomes, e.g. number of families screened, proportion eligible for inclusion, and proportion consenting to participate.

The primary comparison of the trial arms will use an intention-to-treat framework. A regression analysis will be undertaken to quantify the extent to which a potential intervention effect on the primary outcome is determined by allocation to the intervention. Per-protocol comparison will be performed as a secondary analysis. Further moderation analyses will examine the associations between outcomes and participants’ characteristics. Differences in the means and proportions on measures between T2 and T3 will be assessed using parametric and non-parametric tests.

The cost-effectiveness analysis will compare the two arms of the trial at T2 follow-up using capability-adjusted life-years (CALY) gained as the outcome of interest. To analyse the cost differences between the two arms, we will collect information about intervention costs (i.e. personnel time, material, etc.) and societal resource use. We will express the final output as a cost/ CALY. Results will be presented as incremental cost-effectiveness ratios (ICER, expressing the cost per additional CALY gained). Uncertainty will be demonstrated using a cost-effectiveness acceptability curve, using bootstrapped regression estimates [5].

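### The stated 142 families in total (71 per group) is half of what the plan's own inputs require for 80% power; the figure should be about 142 per group

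*Protocol article*

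**What the plan says.** The Sample size section bases the target on the primary analysis, a between-arm comparison of the mean number of child material and social deprivation (MSD) items lacked at T2, three months after randomisation. The inputs are all given: "Using a significance level of 0.05 and 80% power", a 1-item difference, and "assuming a standard deviation of 3". The result is that "a total of 142 families (71 per group) will be required to detect a 1-item group difference". The section then gives a separate attrition projection ("Loss to follow-up is projected at 50"%) and refers to Fig. 2 for the projected numbers.

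The Design section fixes the comparison as parallel and equally allocated: "A two-arm randomised waitlist-control superiority trial (1:1 allocation ratio) will be conducted". The Statistical methods section describes the primary model only in general terms: "A regression analysis will be undertaken to quantify the extent to which a potential intervention effect on the primary outcome is determined by allocation". The article names no covariates, no T1–T2 correlation and no one-sided test.

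**The concern.** The article states every input to a textbook sample size calculation and an answer that does not follow from them. The number given as the total is the number needed in each arm.

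This is the only power statement in the article, and it concerns the only primary outcome. The Discussion describes the trial as a step that must precede any recommendation for national implementation. If readers believe the trial had 80% power for a 1-item difference when the stated calculation gives about 50%, a non-significant result could be taken as evidence that the model does not work. On the calculation as stated, a true 1-item effect would be missed about half the time.

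**Working it through.** **Inputs (Sample size and Design sections).** Difference δ = 1 item; SD σ = 3; alpha 0.05, sidedness not stated, taken as two-sided and then tried one-sided; power 80%; two independent arms, 1:1.

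**Step 1. Try to reproduce the stated figure.** For two independent means,

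n per group = 2σ²(z₁₋α/₂ + z₁₋β)² / δ²

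with (1.960 + 0.842)² = 7.849, so n = 2 × 9 × 7.849 / 1 = 141.3, rounded up to **142 per group, 284 in total**. The two-sample t-test (noncentral t) gives 142.2, rounded up to 143 per group, 286 in total. The plan's 142 in total is not reproduced; it equals the per-group number.

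**Step 2. Power at the stated size.** With 71 per group the standard error of the difference is 3 × √(2/71) = 0.5035, so δ/SE = 1.986. Power is Φ(1.986 − 1.960) = 51.0% by the normal approximation and 50.5% by the t-test.

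**Step 3. Difference detectable with 80% power at 71 per group.** (1.960 + 0.842) × 0.5035 = 1.41 items (normal); 1.42 items by the t-test.

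**Step 4. Could another reading give 71 per group?**

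| Reading | Result |
|---|---|
| One-sided alpha 0.05 | 112 per group (224 in total); power at 71 per group is 63% |
| One-sample or paired formula, 9 × 7.849 | 70.6, so 71; but this is not a comparison of two arms |
| Smaller SD | 71 per group gives 80% power if the SD is about 2.1, not 3 |
| Adjustment for the T1 score, SD × √(1 − r²) | needs a T1–T2 correlation r of about 0.71 |
| Change score, variance 2σ²(1 − r) | needs r of about 0.75 |

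The article states none of the last three, and the first two do not rescue the figure.

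**Step 5. What T1 adjustment would give at 71 per group (t-test).** The correlations are illustrative assumptions; none is in the document.

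| r | Power |
|---|---|
| 0 | 50.5% |
| 0.3 | 54% |
| 0.5 | 62% |
| 0.6 | 69% |
| 0.7 | 79% |
| 0.71 | 80% |

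**The case against.** The arithmetic has no good defence: no input is hidden, and nothing elsewhere in the article corrects the figure. Three stronger conclusions are tempting, however, and the document does not support them.

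*The trial as it will be analysed has only 50% power.* The 50% belongs to the unadjusted calculation on the stated inputs. The primary analysis is a regression whose covariates the article does not list; they may be set out in an analysis plan not shown here. The MSD measure is collected at T1, so adjustment is possible and could recover some power. This part of the objection stands and limits the claim. It does not restore the 80%, because the published calculation uses SD 3 and assumes no correlation.

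*Attrition makes matters worse still.* A reader might take 142 as the number randomised, apply the projected 50% loss, and arrive at about 35 analysed per arm and about 28% power. A reader might also object that the text does not say whether 142 is before or after loss. Fig. 2 carries the projected numbers and is not visible in the text reviewed, so neither point can be held against the plan. The number required to detect a difference is in any case most naturally read as families analysed.

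*The factor of two for two groups was dropped.* The one-sample formula does give 71. But the same figures would arise if 142 per group had been computed correctly, then read as a total and halved. The document does not show which happened.

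**Conclusion.** The figure is wrong as written. A two-arm comparison of means with a 1-item difference, SD 3, two-sided alpha 0.05 and 80% power needs about 284 to 286 analysed families, twice the stated 142. This finding rests only on inputs that the article itself states, and on reading alpha as two-sided; a one-sided reading still leaves the total well short (224 needed). The 50% power and the detectable difference of about 1.4 items apply to 71 analysed per group without covariate adjustment. This is not a matter of detail left to a fuller document: further detail could replace the stated assumptions, but it cannot make the stated ones yield 71 per group.

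**What to change.** Correct the sentence in the Sample size section to say that about 142 families per group, 284 in total, analysed at T2 are required for 80% power to detect a 1-item difference with SD 3 at two-sided alpha 0.05 (normal approximation; 143 per group, 286 in total, if the t-test is the named method).

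If 142 analysed families remains the target, state what it delivers without adjustment: about 50% power for 1 item, or 80% power for about 1.4 items.

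If the sponsor relies on adjustment for the T1 score, replace the calculation with the adjusted one and give the assumed T1–T2 correlation with a source outside this trial. About 0.71 is needed to keep 80% power at 71 per group. It should not be adopted simply because it reproduces the target.

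**Cost.** Restating the figure is a change of text and needs no extra families, but the stated power or detectable difference becomes less favourable. Keeping 80% power for 1 item without adjustment needs about twice as many analysed families; if the projected 50% loss applies up to T2, 284 analysed means 284 / 0.5 = 568 randomised.

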### Randomisation

A computer-generated randomisation sequence will be used to assign the participants to the intervention and waitlist-control arms in a 1:1 ratio. Block randomisation will be generated in a computerised randomisation schedule. Separate randomisation lists will be created for each BVC site. Randomisation will take place after pre-intervention data collection. The allocation sequence will be concealed using an online central randomisation service set up and maintained by a professional third party (www.sealedenvelope.com) that will conceal the sequence until group assignment. The randomisation process will require the research team to log into a password-protected website and enter the relevant data of each newly recruited participant in order to receive the allocation. The research team will inform the participant of the randomisation outcome – that they will be referred to the municipal budget and debt counselling straight away or after a period of 3 months.

### Blinding

Randomisation will take place at the research institution, conducted by the research team, directly after T1 data collection. Allocation status will be recorded on the randomisation website, and emailed to the research team member conducting the randomisation [name] and the trial manager [name]. Participants will not be blinded to group allocation, and data collection will not be blinded. Given that neither participants nor budget and debt counsellors are blinded, there is no requirement for an unblinding procedure. Questionnaire data spreadsheets will use participant identity numbers; however, group status will be apparent due to the inclusion of counselling session attendance data for the intervention group.

### Intervention arm

*All* participants will be given a copy of *‘Your child, your money’*, a freely available financial guidance book for new parents at the time of screening. The book has been developed by Finansinspektionen, Sweden's financial supervisory authority, and covers topics such as planning finances, consumer rights, private insurance, family law, parental leave, pensions, saving, and budgeting. (see Table 1 for an overview of content). Participants randomised to the intervention arm will be immediately referred to the local budget and debt counselling service. After receiving the participants’ details, first contact from a budget and debt counsellor will take place within a few weeks. Budget and debt counselling will involve at least one meeting with a counsellor. Examples of assistance the counsellors can offer include: suggestions on ways to improve a participant’s financial situation; checking eligibility and helping to apply for social welfare support; helping to organise finances and develop a budget; and assistance with debt management, threatening letters or harassment by debt collectors, or imminent house eviction. The municipal budget and debt counselling services involved in the trial will receive guidance on how to work preventatively with families, which prompts discussion on needs, personal goals, financial behaviour and income maximisation. Participants may end counselling at any time, and there will be no restrictions on access to other support during the study period.

**Table 1 Tab1:** Overview of’Your child, your money’ content

Pregnant	Parent	Family
- Plan your economy - Plan for new costs - Your rights as a consumer - Private insurance - Family legislation	- Parental leave - Our pension system - Parental leave and studies - Child insurance - To save for children	- Child sickness - Links - My monthly budget

### Control arm

As described above, all participants receive a copy of the book. Those randomised to the waitlist control arm will be referred to the local financial counselling service after a period of 3 months.

### Participant timeline

Figure 2 provides an overview of the participant timeline. Parents/caregivers are screened for eligibility at a routine BVC appointment. Screening data will be automatically transferred to the research team via a secure online platform. When a parent screens positive and indicates they are interested in participating in the project, a member of the research team will contact them to complete the informed consent procedure and the study questionnaire. A case will be randomised once all pre-intervention data has been collected. Follow-up data will be collected from all participants at scheduled group meetings at two points: 3 months after randomisation (T2) and 12 months after randomisation (T3).

### Measures

The primary outcome measure for the RCT is child material and social deprivation (MSD). Secondary measures include household income and sources of income, financial knowledge, financial control, readiness to change, personal goal attainment, parental mental health, and financial stigma. These measures will be administered at all time points and assessed at T2 (for the RCT) and T3 (for the longitudinal cohort study). See Fig. 3 for an overview of the enrolment, intervention and assessment schedule.

**Fig. 3 Fig3:**
[figure not shown]
Schedule of enrolment, interventions and assessments

Due to the target population being both Swedish speaking and non-Swedish speaking, there will be translated measures available in the data collection process. Translated measures will be provided for the larger language groups at each project site. For some measures, there are translated versions readily available. For the other measures, we will use a certified translation service. For validation, back-translations will be conducted.

#### Child MSD

The European Union (EU) measure of child MSD [8] contains 17 items; 13 child-specific items (e.g. *Two pairs of properly fitting shoes; Celebrations on special occasions*) and 4 household items (e.g. *Home adequately warm; Access to the Internet*). Parents are asked to indicate whether or not they have the item. If not, they are asked if it is because they cannot afford it (enforced lack) or for another reason (simple lack). Data are collected at the household level; if one child does not have an item it is assumed that all the children in the household lack that item. Cronbach’s alpha indicates adequate reliability of the ‘enforced lack’ concept in Sweden (α = 0.76) and across EU countries (α = 0.76–0.94) [8]. The items have been shown to be additive, i.e. a household with a score of “2” is in reality suffering from more severe MSD than a household with a score of “1” or a score of “0” [8]. As recommended by Gui et al. (2018), an unweighted sum of the 17 MSD items will be calculated for each household in the trial. The primary analysis for the RCT will be a comparison of the unweighted mean number of child MSD items lacked at T2. A secondary outcome of the trial will be a comparison of the proportion of children classified as experiencing deprivation at the 3-month follow-up. As reported by Gui et al. [8], a threshold of 3 items will be applied to the data. In other words, a household lacking two or less items will be classified as ‘*not* experiencing deprivation’ and a household lacking three or more items will be classified as ‘experiencing deprivation’. Both the unweighted mean number of child MSD items lacked and the proportion of children classified as experiencing deprivation will also be assessed at T3 as part of the longitudinal follow-up.

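### The stated primary analysis compares mean T2 deprivation counts and specifies no adjustment for the T1 count or the BVC stratification factor, though both are known for every randomised family

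*Protocol article*

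**What the plan says.** Three sections of the protocol article describe the primary analysis.

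- **Child MSD** (under Measures): "The primary analysis for the RCT will be a comparison of the unweighted mean number of child MSD items lacked at T2". The Sample size section says the same and states that the target number was derived from this analysis.
- **Sample size**: "a total of 142 families (71 per group) will be required". The target is a difference of one item between the arms, and the SD is taken as 3. No T1-T2 correlation and no variance reduction from covariates is mentioned.
- **Statistical methods**: the primary comparison is by intention to treat, and a regression is planned: "A regression analysis will be undertaken to quantify the extent to which a potential intervention effect on the primary outcome is determined by allocation". No covariate is listed. Participant characteristics enter only in the later moderation analyses.

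Two design features bear on this. The Measures section says of the primary and secondary measures: "These measures will be administered at all time points and assessed at T2 (for the RCT". The Participant timeline section has a case randomised only after its pre-intervention data are complete, so every randomised family should have a T1 deprivation count. The Randomisation section says "Separate randomisation lists will be created for each BVC site", which makes BVC site a stratification factor.

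**The concern.** The outcome is a count of items lacked by the same household, measured before randomisation and again three months later. If the two counts are correlated, part of the T2 variance is predictable from T1, and a comparison of T2 means leaves that part in the error term. It also leaves uncorrected any T1 difference between the analysed arms, whether from chance or from loss to follow-up, which the article projects at 50%. The second kind of difference is addressed only as far as loss depends on the observed T1 score.

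Stratifying by BVC and then leaving site out of the model makes the standard error slightly too large, so the test is mildly conservative.

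Pre-specification matters too. The Blinding section says that group status will be apparent in the data spreadsheets. If the covariates are not fixed in advance, a raw and an adjusted result can both be produced by people who can see allocation, with nothing in the article to say which is primary.

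**Working it through.** **Inputs from the Sample size section.** Difference 1 item; SD 3; "Using a significance level of 0.05 and 80% power"; 71 per arm. Sidedness is not stated, and two-sided is used here. Allocation is 1:1 (Design section).

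**Assumed, because the article gives no value.** T1-T2 correlation r from 0.3 to 0.8; share of outcome variance due to BVC site from 1% to 10%.

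**Step 1: the plan's own figure.** n per arm = 2 × SD² × (z₀.₉₇₅ + z₀.₈₀)² / δ² = 2 × 9 × (1.960 + 0.842)² / 1 = 141.3, so 142 per arm and 284 in total (142.2 per arm with the t distribution). One-sided, it is 112 per arm. Neither gives 71 per arm. The stated total of 142 equals the two-sided number for one arm.

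**Step 2: power of the stated comparison at 71 per arm.** Standard error = 3 × √(2/71) = 0.5035. Power = Φ(1/0.5035 − 1.960) = Φ(0.026) = 51.0% (50.5% with the t distribution; 63.4% if one-sided).

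**Step 3: adjusting for the T1 count.** The residual SD is 3 × √(1 − r²). For r = 0.5 it is 2.598, the standard error is 0.436, and power = Φ(1/0.436 − 1.960) = Φ(0.333) = 63.1%.

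| Assumed r | Residual SD | Power at 71 per arm | n per arm for 80% |
|---|---|---|---|
| unadjusted | 3.000 | 51.0% | 142 |
| 0.3 | 2.862 | 54.9% | 129 |
| 0.5 | 2.598 | 63.1% | 106 |
| 0.6 | 2.400 | 69.9% | 91 |
| 0.7 | 2.142 | 79.4% | 73 |
| 0.8 | 1.800 | 91.2% | 51 |

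For 71 per arm to give 80% power, r² must be 1 − 71/141.3 = 0.497, so r of about 0.71.

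**Step 4: adjusting for site only.** The residual SD is 3 × √(1 − site share). Power at 71 per arm is 51.4%, 51.8%, 53.1% and 55.3% for shares of 1%, 2%, 5% and 10%. If site is ignored at a 5% share, the nominal 5% test has a type I error of about 2 × (1 − Φ(1.960/√0.95)) = 4.4%.

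**Step 5: if 142 is the number randomised and half are lost.** About 35.5 per arm are analysed. Power is 28.9% unadjusted, 36.8% at r = 0.5 and 50.3% at r = 0.7. The article's text does not settle whether 142 is the number randomised or analysed, and the numbers in its Fig. 2 are not shown.

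**The case against.** The strongest objection is that the article is silent on covariates and does not reject them. A reader might infer that the regression is on allocation alone and that the primary result will certainly be unadjusted. The documents do not support that. The Statistical methods section neither lists nor excludes covariates. A baseline-adjusted regression also estimates a difference in T2 means, so it is compatible with the Sample size and Child MSD sections. The word unweighted there refers to the sum of the 17 items. Sizing on a raw SD can simply be conservative. A covariate list may also sit in a full protocol or analysis plan that is not shown. All of this stands, and it is why the point is that no adjustment is specified.

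It does not remove the point. The article defines the primary analysis twice as a comparison of T2 means, sizes the trial on it, and then describes a regression without saying how the two relate. If an unseen plan does adjust, these sections should say so.

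Two further inferences should be resisted. One is that missing adjustment causes the low power: the 51% comes from the sample-size arithmetic in Step 1, a separate error. The other is that adjustment would restore 80%: that needs r of about 0.71 with all 142 families analysed, and at r = 0.3 the gain is about four percentage points.

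The site component is also minor, and including site has a small cost, since some BVC strata may be sparse after the projected loss.

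**Conclusion.** The point holds as a weakness in how the primary analysis is fixed, and it should be corrected. As written, the primary analysis is a T2 comparison with no specified use of the T1 count or the stratification factor.

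Over assumed correlations of 0.3 to 0.7, adjusting for T1 adds roughly 4 to 28 percentage points of power at 71 analysed per arm. How much of that would be realised cannot be said from the article. Including site mainly matches the analysis to the randomisation.

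The figures assume a two-sided 5% test, the normal approximation, SD 3 in both arms and a linear T1-T2 relation common to both arms.

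**What to change.** In Statistical methods, state the primary analysis as a linear regression of the T2 MSD count on arm and T1 MSD count, with BVC site included as a random intercept or with small sites pooled by a rule set in advance. Name the arm coefficient with its 95% confidence interval as the primary result. Reword the Sample size and Child MSD sections to refer to this model, and keep the raw T2 mean difference as descriptive.

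The cost is a sentence or two and a rule for sparse sites. No new data are needed, and the target remains a difference in mean T2 items lacked. The change should be made before outcome data are analysed by arm.

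The sample size needs its own correction. If the sponsor wishes to take credit for T1 adjustment there, the assumed correlation should be stated and justified.
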